## **I. Sample Size Estimation**

The primary hypothesis of this study is that enhanced targeted HIV screening will be significantly associated with new HIV diagnoses when compared to nontargeted HIV screening. As described above, the primary statistical measure will include an unadjusted RR. Based on our *a priori* assumptions related to the performance of each screening method weighted across the four study sites (i.e., nontargeted screening – 25% HIV test completion, 0.3% HIV test prevalence; enhanced targeted screening – 5% HIV test completion, 2% HIV test prevalence), we anticipate requiring a minimum of 12,600 HIV tests performed to achieve a statistically significant association using an alpha of 0.05 (i.e., estimated unadjusted RR = 1.33, 95% CI: 1.01-1.79). We also anticipate adjusting variance estimates to account for within-institution correlation; as such, we will plan to complete at additional 10%, resulting in a total of 14,000 HIV tests performed.

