## **H. Analytic Plan**

All statistical analyses will be conducted by the Principal Investigator and independently confirmed by the study's biostatistician blinded to study allocation. Final analyses will be performed after cleaning and locking of the dataset. Although no formal interim analyses are planned, the study team may perform preliminary analyses for purposes of presentation at scientific meetings; these instances, if they occur, will be explicitly described as preliminary and qualified as such.

### Specific Aim 1

Descriptive analyses will be performed for all variables. Continuous data will be reported as means with standard deviations (SDs) or medians with interquartile ranges (IQRs), depending on whether they are normally distributed or non-normally distributed, respectively; additionally, categorical data will be reported as proportions or percentages with 95% confidence intervals (CIs). Bivariate statistical tests (e.g., Student's t-test or Wilcoxon rank sum test for two-group parametric or non-parametric comparisons, ANOVA or Kruskal-Wallis test for three-group parametric or non-parametric comparisons, and chi-square test or Fisher's exact test) will be used to compare variables between study groups. Patient-level data will be reported for demographics. Otherwise, patient-visit data will be reported given the relatively large degree of recidivism to EDs; as such, the primary unit of analysis will be patient visits.

All analyses will be performed using the intention-to-treat principle and no interim analyses are planned given the "pragmatic" trial approach and minimal risk to subjects. Given the randomized controlled trial design, the primary comparison will include unadjusted risk ratios (RRs) for newly-identified HIV infection (primary outcome) with 95% CIs, specifically comparing enhanced targeted HIV screening to nontargeted HIV screening (the primary hypothesis of this study). Statistical significance for the primary analysis will be defined as  $<0.05$  based on two-tailed statistical testing, which includes a lower 95% confidence limit of  $>1.0$ .

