## C. Number and Distribution of Subjects

As described above, enrollment will proceed until approximately 3,500 HIV tests are performed per site, for a total of 14,000 HIV tests. Therefore, it is estimated that up to 30,000 subjects per site will be included in this project, resulting in up to 120,000 total subjects included across all four sites. This will represent the largest ED-based HIV screening study to-date and the first to evaluate these three standard-of-care approaches. This will also allow each site to begin and end enrollment without committing to a specific time period (i.e., some sites may complete enrollment in 6 months, whereas other sites may require 10 months, depending on screen positive and HIV test completion rates) (**Figure 2**).

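### The planned 12,600 HIV tests do not give the stated 95% CI of 1.01-1.79: on the protocol's own inputs the expected interval is about 0.84-2.12, with power about 23%

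*Protocol*

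**What the plan says.** The Sample Size Estimation section (4.I) gives the inputs as "nontargeted screening – 25% HIV test completion, 0.3% HIV test prevalence" and "enhanced targeted screening – 5% HIV test completion, 2% HIV test prevalence". From these it concludes "we anticipate requiring a minimum of 12,600 HIV tests performed to achieve a statistically significant association", with the expected result "estimated unadjusted RR = 1.33, 95% CI: 1.01-1.79". It then adds 10% for correlation within institutions, which brings the total to 14,000 tests. It states no power and no completion rate for the traditional targeted arm.

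The Analytic Plan (4.H, Specific Aim 1) compares enhanced targeted with nontargeted screening by an unadjusted risk ratio under intention to treat, and says "the primary unit of analysis will be patient visits". Significance is judged at 0.05, "based on two-tailed statistical testing, which includes a lower 95% confidence limit of" more than 1.0.

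Section 5.C says "enrollment will proceed until approximately 3,500 HIV tests are performed per site, for a total of 14,000 HIV tests". It estimates that this will involve at most 30,000 subjects per site and 120,000 overall. Allocation is 1:1:1.

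**The concern.** New diagnoses are rare on the visit scale: 0.075% and 0.100% of randomised visits under the protocol's assumptions. The width of the interval is therefore set almost entirely by the number of diagnoses. A ratio of 1.33 with a lower limit above 1 needs diagnoses in the high tens to low hundreds per arm, and 12,600 tests at the stated prevalences do not yield that many.

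This is the only statement in the protocol that the trial is large enough for its primary hypothesis. If it is wrong, the sponsor and readers believe that the trial should succeed when enhanced targeting performs as assumed. On the same assumptions it would miss significance roughly four times in five.

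**Working it through.** **Inputs.** From section 4.I: nontargeted arm 25% completion and 0.3% test prevalence; enhanced targeted arm 5% and 2%; 12,600 tests, raised to 14,000; alpha 0.05. From 4.H: visits as the unit of analysis, two-sided test, lower limit above 1. From 5.C: 14,000 tests and up to 120,000 subjects.

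**Step 1: what reproduces.** Diagnoses per visit = completion x prevalence.
- Nontargeted: 0.25 x 0.003 = 0.00075.
- Enhanced targeted: 0.05 x 0.02 = 0.00100.
- RR = 0.00100 / 0.00075 = 1.33, as stated. Per test the ratio would be 0.02 / 0.003 = 6.67, so the plan's RR is per randomised visit, in line with 4.H.
- 12,600 / 0.9 = 14,000, as stated.

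**Step 2: visits per arm.** With equal allocation, visits per arm = tests / sum of the arms' completion rates.
- Stated inputs only, with all tests in the two primary arms: 12,600 / (0.25 + 0.05) = 42,000.
- Three arms: the third arm's rate has to be inferred. 14,000 / 120,000 = 11.67% = (25% + 5% + 5%) / 3, which implies about 5%. Then 12,600 / 0.35 = 36,000 and 14,000 / 0.35 = 40,000.

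**Step 3: expected interval and power.** SE of ln RR = sqrt(1/a + 1/b - 2/n), where a and b are the expected diagnoses and n is visits per arm. The CI is 1.333 x exp(±1.96 SE). Power ≈ Φ(ln 1.333 / SE - 1.96), with ln 1.333 = 0.2877.

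| Case | Visits per arm | Diagnoses | SE | 95% CI | Power |
|---|---|---|---|---|---|
| 12,600 tests, two arms | 42,000 | 31.5 vs 42 | 0.236 | 0.84-2.12 | 23% |
| 12,600 tests, third arm 5% (inferred) | 36,000 | 27 vs 36 | 0.254 | 0.81-2.20 | 20% |
| 14,000 tests, third arm 5% (inferred) | 40,000 | 30 vs 40 | 0.241 | 0.83-2.14 | 22% |

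Simulation with 200,000 replicates gave 22.6%, 19.8% and 21.3% for the three rows.

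**Step 4: what the stated interval would need.** Its width implies SE = ln(1.79 / 1.01) / (2 x 1.96) = 0.146. Then n = (1/0.00075 + 1/0.00100 - 2) / 0.146² ≈ 109,000 visits per arm, with about 82 versus 109 diagnoses. Matching one limit instead of the width moves n between about 103,000 and 116,000. At 109,000 per arm the two primary arms alone would produce about 33,000 tests. Power there is Φ(0.2877 / 0.146 - 1.96) ≈ 50%, as it must be when the lower limit sits almost at 1 under the assumed effect.

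**Step 5: other readings tried.**
- A 90% interval still includes 1: 0.88-2.03 at 36,000 visits per arm.
- All 12,600 tests in the nontargeted arm gives 50,400 visits per arm and 0.88-2.03.
- All 12,600 tests in the enhanced arm gives 252,000 visits per arm and 1.10-1.61. This excludes 1, but it is not 1.01-1.79 and cannot be squared with 14,000 tests in total or 120,000 subjects.
- Tests as the denominator gives an RR of 6.67, not 1.33.

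**Step 6: detectable effect.** At 40,000 visits per arm with the nontargeted rate held at 0.00075, power is 78-79% at RR 1.85 and 81-83% at RR 1.9, depending on the approximation. The RR detectable with 80% power is therefore about 1.9.

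**The case against.** The best objection is that the three-arm figures use a completion rate that section 4.I does not give. It is back-calculated from an upper estimate of enrolment. That is right, and so the two-arm figure comes first. It uses stated inputs alone and is the most favourable split across the arms, since any test in the traditional arm lowers the number of visits. The lower limit is still 0.84.

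It can also be said that the section promises no power, so power of 20-23% contradicts nothing. That is so. The error is the interval and the claim of significance resting on it; power only shows the size of the gap.

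A reader might infer more than the documents support:
- **That closing on tests is a flaw and sites should close on visits.** Section 5.C adopts the test-based rule openly because completion rates differ between sites, and the rule protects the yield when completion is low. If all completion rates were one-fifth lower (20%, 4%, 4%), 14,000 tests would mean 50,000 visits per arm, still 30 versus 40 diagnoses and 22% power. A fixed 40,000 visits per arm would give 24 versus 32 and 19%. A busier traditional arm pulls the other way. This is a trade-off, and 120,000 is an upper estimate, not a target.
- **That the 10% allowance is an error.** Section 4.I ties it to the variance estimate, and 4.H plans secondary models for clustering by institution and patient. It is a small margin that does no harm.
- **That the pilot in section 3 points to no effect.** It reports equal numbers of diagnoses but no denominators, so it does not give a per-visit RR.
- **How the wrong interval arose.** Putting 108,000 visits, the three-arm total for 12,600 tests (3 x 36,000), into each arm gives 1.00-1.78, close to the stated interval. That is a possible explanation, but the protocol does not say it.

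**Conclusion.** The point holds. The stated interval and the claim of significance do not follow from the section's own inputs. The stated interval needs 2.6 times (109,000 / 42,000) to 3 times (109,000 / 36,000) the visits per arm that 12,600 tests can supply.

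The two-arm result rests only on the stated rates, equal allocation and the usual large-sample interval for a risk ratio. The three-arm and 14,000-test results also assume about 5% completion in the traditional arm; higher completion there would make them worse. The conclusion concerns what the protocol claims about its size. It does not show that the closing rule, the 10% allowance or the choice of primary comparison is wrong.

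**What to change.** In section 4.I, replace the interval and the statement that 12,600 tests suffice for significance with the figures for the planned size: 14,000 tests, about 40,000 visits per arm, 30 versus 40 expected diagnoses, RR 1.33, 95% CI about 0.83-2.14, power about 22%, and an RR of about 1.9 detectable with 80% power. State the roughly 5% completion in the traditional arm as an assumption, since visits per arm depend on it.

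This changes protocol wording only. Enrolment, the closing rule and the 10% allowance stay as they are. The cost is that the stated precision becomes much less favourable. The correction discloses the trial's power; it does not raise it.

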## 5. HUMAN SUBJECTS PROTECTION

### A. Description, Risks, and Justification of Procedures

#### Recruitment Methods

All patients who present to the ED during the study periods, and who meet eligibility criteria, will be included. Patients who meet eligibility criteria will be randomized to one of three screening interventions that will be integrated into the electronic patient tracking systems. Randomization will occur automatically during implementation of standard-of-care triage via programming integrated into the electronic patient tracking and triage systems. Eligible patients assigned to the nontargeted HIV screening arm will be offered on-site, voluntary, and confidential rapid HIV testing by nurses using opt-out consent during medical screening (triage) examination. Patients assigned to the enhanced targeted HIV screening arm will be asked the refined DHRS questions during the medical screening (triage) examination. Patients in this group who are categorized as “high risk” (defined as a refined DHRS score  $\geq 30$ ) will be offered on-site, voluntary, and confidential rapid HIV screening by nurses using opt-out consent. Patients who are assigned to the traditional targeted HIV screening arm will be asked the BRST questions during the medical screening (triage) examination. Patients in this group who are categorized as “high risk” (defined as a BRST score  $\geq 1$ ) will be offered on-site, voluntary, and confidential rapid HIV screening using opt-out consent. Patients assigned to the two targeted HIV screening arms and identified as “low risk” (defined either as a refined DHRS  $\leq 30$  or a BRST score = 0) will not be routinely offered rapid HIV testing; however, they will be eligible for diagnostic HIV testing by their treating physicians. Similarly, patients assigned to the nontargeted HIV screening arm but who decline HIV testing will also be eligible for diagnostic HIV testing by their treating physicians.

During study enrollment, an HIV informational form about HIV infection will be made available to patients (see “**Denver Health Information about HIV**” in the **Appendix**). The Denver Health informational sheet will be adapted for each study site. Also, during the entire study period, all patients who test positive for HIV infection will undergo structured posttest counseling by dedicated clinical social workers. These patients will be offered the opportunity to participate in the follow-up portion of this study (see below). All staff offering testing to patients will have a treatment relationship with the patients. Women and minorities will be included in this study without exception.

#### Consent Procedures

All patients who present to the ED at DHMC during this project will receive standard-of-care medical evaluation and treatment and may be asked questions about their risk for HIV infection, using either the refined DHRS or the BRST instruments, and may be offered, as voluntary and routine practice, rapid HIV testing using an opt-out mechanism. Consent for rapid HIV testing will be documented in the patient’s medical record, as it is currently done as part of standard of care. The medical care for those patients who do not receive rapid HIV testing will not vary from those who do, except that the physician will know each patient’s HIV test result and may alter the medical evaluation based on this additional information. Because rapid HIV testing is a standard-of-care in the ED at DHMC (and the other study sites) and because this project will be evaluating three processes for performing HIV screening in this clinical setting (i.e., nontargeted vs. two targeted screening methods), this potential change in care is consistent with current medical practice.

We are requesting a waiver of consent for everyone included as part of the evaluation of the three HIV screening strategies. This request for waiver is based on the following in accordance with 45\_CFR\_46.116(d)(1-4):

- (1) This part of the study is minimal risk because the only risks include breach of confidentiality and possible risks of change from standard of care (although each screening method is consistent with recommended national or local standards of care). The most significant risk to patients will be loss of confidentiality, which is viewed as minimal. All of the methods utilized in this study are currently accepted, recommended and utilized methods for HIV screening, locally or nationally. Furthermore, there is minimal difference in risk between the 3 screening interventions. While there is a potential risk associated with missed opportunities for HIV diagnosis, we believe that this potential risk is also minimal. We also believe that clinical equipoise exists in that there is no empiric evidence that one HIV screening method is superior than another despite policy statements (e.g., CDC and USPSTF) that suggest otherwise; the effectiveness of HIV screening is even more uncertain in ED settings. All medical centers in Colorado, including Denver Health Medical Center, are required by state law to report all diagnoses of HIV infection to the state health department. Patients who access testing services in routine health care settings are exposed to this same risk. Therefore, the risks involved in this study are no more than what the patient would experience in standard care. The Principal Investigator will assume full responsibility for the protection of all study-related documents and datasets, including those that contain protected health information. The Project Coordinator and Principal Investigator will oversee all data collection. All electronic data will be held in an electronic database (Microsoft SQL, Microsoft Corporation, Redmond, WA) using the protected network at DHMC. The database will be password protected and stored in the Project Coordinator's network user a separate folder on the DHMC mainframe network. This network includes firewall protection and the folder can only be accessed by members of the study team. All paper documents will be stored in a locked file cabinet in the Project Coordinator's office. These data will be manually entered into the main electronic database. During this project, all data will be kept in secure locations either in the ED, the office of the Principal Investigator, the office of the Project Coordinator, the office of the clinical social workers, or in the laboratory;
- (2) It does not violate patients' rights (the research will offer HIV testing by asking standard-of-care questions but the patient will still be able to decide whether HIV testing occurs). The risks involved in this study are no more than what the patient would experience in standard care and each patient will be able to decide whether HIV testing occurs;
- (3) Separate written informed consent cannot practicably be carried out without a waiver because of the large number of consecutive patients included from a busy ED, and the potential for biased participation in the study. It is essential that we have 100% participation in this study in order to identify the rate of newly-diagnosed HIV infection, which is the primary outcome for this study. We believe this waiver of consent will not adversely affect the rights and welfare of the subjects involved in this project, as they will only be subjected to current standards of care and they will all have the right to refuse HIV testing ; and
- (4) Each patient will have an experience that does not differ significantly from usual care.

We will obtain written informed consent from all patients who test preliminarily positive for HIV infection in the ED (this number will represent approximately 0.5% of all patients tested for HIV infection, and less than 0.1% of all ED patients overall) in order to obtain additional data including specific behavioral risks and data regarding follow-up with medical and preventive care referrals for up to 1 year following

diagnosis. During posttest counseling, the clinical social workers, all of whom will have completed IRB training, will obtain this consent. This process will take place in a quiet and unhurried setting in the patient's room. The patient will be given enough time to ask questions about the collection of follow-up data. The patient's comprehension will be assessed by asking the patient to describe the follow-up procedures in their own words and a copy of the executed consent form will be provided to the patient. If limited chart abstraction will be performed in lieu of a more detailed patient contact and chart review, a waiver of consent will be obtained for the longitudinal follow-up portion of the study and chart abstraction will be conducted retrospectively.

### Special Consent Issues

As described in "Consent Procedures", we are requesting that separate research consent not be obtained for this study. Separate research consent will be obtained for the follow-up portion of the study if applicable. Pregnant women and prisoners will not be excluded from this study. Pregnant women and prisoners are routinely tested for HIV infection at all study sites.

### *HIV Testing Consent Process (Standard of Care)*

Patients who are  $\geq 16$  years of age will also not be excluded; therefore children may be potentially enrolled in this study. Under current laws in Colorado, California, Maryland, and Ohio (see below), minors are allowed to consent for HIV testing and treatment and other sexually transmitted infections without parental consent. To be consistent with these laws, patients who are under the age of 18 years of age and agree to rapid HIV testing during this study will be able to do so without parental consent as standard of care.

### Colorado State Section Code §25-4-402 (4)

Any physician, upon consultation by a minor as a patient and with the consent of such minor patient, may make a diagnostic examination for sexually transmitted infection and may prescribe for and treat such minor patient for sexually transmitted infection without the consent of or notification to the parent or guardian of such minor patient or to any other person having custody of or parental responsibilities with respect to such minor patient.

### Colorado Revised Statute §25-4-1405 (6)

(6) Any local health department, state institution or facility, medical practitioner, or public or private hospital or clinic may examine and provide treatment for HIV infection for any minor if such physician or facility is qualified to provide such examination and treatment. The consent of the parent or guardian of such minor shall not be a prerequisite to such examination and treatment. The physician in charge or other appropriate authority of the facility or the licensed physician concerned shall prescribe an appropriate course of treatment for such minor. The fact of consultation, examination, and treatment of such a minor under the provisions of this section shall be absolutely confidential and shall not be divulged by the facility or physician to any person other than the minor except for purposes of a report required under sections 25-4-1402 and 25-4-1403 and subsection (8) of this section and a report containing the name and medical information of the minor made to the appropriate authorities if required by the "Child Protection Act of 1975", part 3 of article 3 of title 19, C.R.S. If the minor is less than sixteen years of age or not emancipated, the minor's parents or legal guardian may be informed by the facility or physician of the consultation, examination, and treatment. The physician or other

health care provider shall counsel the minor on the importance of bringing his parents or guardian into the minor's confidence about the consultation, examination, or treatment.

Maryland State section code §20-102 (c3)

A minor has the same capacity as an adult to consent to: (1) treatment for or advice about drug abuse; (2) treatment for or advice about alcoholism; (3) treatment for or advice about venereal disease.

California State section code §121020

(a) (1) When the subject of an HIV test is not competent to give consent for the test to be performed, written consent for the test may be obtained from the subject's parents, guardians, conservators, or other person lawfully authorized to make health care decisions for the subject. For purposes of this paragraph, a minor shall be deemed not competent to give consent if he or she is under 12 years of age.

California State section code §6926

(a) A minor who is 12 years of age or older and who may have come into contact with an infectious, contagious, or communicable disease may consent to medical care related to the diagnosis or treatment of the disease, if the disease or condition is one that is required by law or regulation adopted pursuant to law to be reported to the local health officer, or is a related sexually transmitted disease, as may be determined by the State Public Health Officer.

Ohio State section code §3701.242

(A) An HIV test may be performed by or on the order of a health care provider who, in the exercise of the provider's professional judgment, determines the test to be necessary for providing diagnosis and treatment to the individual to be tested, if the individual or the individual's parent or guardian has given consent to the provider for medical or other health care treatment. The health care provider shall inform the individual of the individual's right under division (D) of this section to an anonymous test.

(B) A minor may consent to be given an HIV test. The consent is not subject to disaffirmance because of minority. The parents or guardian of a minor giving consent under this division are not liable for payment and shall not be charged for an HIV test given to the minor without the consent of a parent or the guardian.

*Follow-Up Research Consent Process*

As described above, patients who are ≥16 years of age will not be excluded; therefore children may be enrolled in this study, agree to HIV testing, and be diagnosed with HIV infection. Under current laws in Colorado, California, Maryland, and Ohio, minors are allowed to consent for HIV testing and treatment without parental consent. Thus, we are requesting patient assent (without parental consent) for those under the age of 18 years who test positive for HIV infection in the ED for the collection of follow-up data relating to HIV treatment. This will be obtained using a written assent form. In cases where study sites choose to do limited chart abstraction in lieu of a more detailed chart abstraction, a waiver of consent will be obtained for the longitudinal portion of the study.

